### Primary Outcome

#### Preschoolers’ PA

The PA level and sedentary time will be objectively monitored using a triaxial accelerometer ActiGraph GT3X-BT (ActiGraph). The ActiGraph accelerometer has been found to be valid and reliable to objectively measure PA levels in preschoolers [72]. The kindergarten teachers and parents will receive written and video instructions for the use of the accelerometer. In addition, parents will be asked to register an activity diary for both wear and nonwear times. The accelerometer wear will be checked by teachers on each school day. An accelerometer will be affixed to the participant’s right wrist to monitor all activities for a period of 7 continuous days, except during periods of water-related activities or situations involving the risk of damage to the device, such as contact sports or self-defense. Data will be downloaded and initialized using the ActiLife software (version 6.13) and analyzed in 1-second epochs. Valid wear time will be considered at least 16 hours of wear time over at least 3 days (2 weekdays and 1 weekend day) [73]. Nonwear time will be defined by 60 consecutive minutes of 0 counts per minute (CPM), using ActiLife standard approaches. The accelerometer’s activity counts will be categorized into different intensities (ie, sedentary behavior, light PA, moderate PA, and vigorous PA) by using cutoff points as follows: sedentary, <819 CPM; light, 820-3907 CPM; moderate, 3908-6111 CPM; and vigorous, ≥6112 CPM.

### Secondary Outcomes

#### Preschoolers’ DB

Preschoolers’ DB will be assessed using the Children’s Eating Behavior Questionnaire (CEBQ), which has been shown to be valid in Chinese preschool-age children [74]. Parents will rate the frequency of their children’s eating behaviors on a 5-point scale (1=never, 2=rarely, 3=sometimes, 4=often, 5=always) in terms of 8 domains (35 items): satiety responsiveness (eg, My child gets full before the meal is finished), slowness in eating (eg, My child finishes the meal quickly), food fussiness (eg, My child enjoys tasting new foods), food responsiveness (eg, If allowed, my child would eat too much), enjoyment of food (eg, My child enjoys eating), desire to drink (eg, If given the chance, my child would always be having a drink), emotional undereating (eg, My child eats more when happy), and emotional overeating (eg, My child eats more when there is nothing else to do). The scale has high internal consistency and reliability (overall Cronbach α >.7).

#### Preschoolers’ Sleep Duration and Problems

The ActiGraph accelerometer will be used to examine children’s sleep duration in conjunction with a parent-reported log sheet and nap schedule provided by kindergartens. Bedtime and wakeup time will be identified based on the algorithm by Sadeh et al [75], and periods of sleep will be estimated using the algorithm by Tudor-Locke et al [76]. The nighttime sleep and daytime nap durations, bedtime, and wakeup time will be assessed using ActiLife software (version 6.13) in 60-second epochs and matched with the nap schedule filled out by kindergarten teachers and log sheets finished by parents. The total duration of sleep per day will be the sum of nighttime and daytime sleep.

The Chinese version of the Children’s Sleep Habits Questionnaire (CSHQ) [77], a parent survey regularly used to track kids between the ages of 4 and 10 years, will be used to assess preschoolers’ sleep problems. It contains 33 items from 8 domains: bedtime resistance, sleep onset delay, sleep duration, sleep anxiety, night waking, parasomnia, sleep-disordered breathing, and daytime sleepiness. Each scored question is rated on a 3-point scale as follows: 3=“usually if something occurs 5 or more times in a week,” 2=“sometimes if something occurs 2-4 times in a week,” and 1=“rarely if something occurs never or 1 time during a week.” Higher scores represent greater sleep problems. This survey has shown good reliability (Cronbach α=.73) and validity.

#### Preschoolers’ Screen Time

Parents will be asked to answer questions that estimate the usual amount of screen time for their children on a typical weekday and weekend to determine the average screen time per week. Questions also involve the availability of screens and rules about screen entertainment. This questionnaire has been used in a previous study [23].

#### Parents’ PA

Parents’ PA will be assessed using the Chinese version of the International Physical Activity Questionnaire-Short Form (IPAQ-SF). The questionnaire will ask about the time spent being physically active in the last 7 days through 7 questions. The obtained data will be converted to metabolic equivalent task (MET) scores for each dimension or intensity of PA. To calculate the weekly PA (MET-min/week), the number of total minutes dedicated to each activity class is multiplied by the specific MET score for the activity, with 3.3 METs for walking, 4 METs for moderate PA, 6 METs for cycling, and 8 METs for vigorous PA. This questionnaire has been shown to be a reliable and validated measure for assessing PA levels in Chinese cities (overall Cronbach α=.788) [78].

#### Parenting Style

The Parenting Style & Dimension Questionnaire, a self-report instrument designed to measure authoritarian (eg, I yell when I disapprove of my child’s behavior), authoritative (eg, I am responsive to my child’s feelings and needs), and permissive (eg, I find it difficult to discipline my child) parenting styles of the parents of children aged 4-12 years, will be used to evaluate the parenting styles. This scale comprises 32 items, with each item of the scale evaluated using a 5-point Likert scale (“never,” “once in a while,” “about half of the time,” “very often,” and “always”). The overall Cronbach α is .87 [79].

#### Parental Feeding Style

The parental feeding style will be assessed using the Chinese version of the Parent Feeding Style Questionnaire, which consists of 4 parts: instrumental feeding (4 items), emotional feeding (5 items), prompting or encouragement to eat (8 items), and control over eating (10 items). Respondents will be asked to choose responses on a 5-point Likert scale (ranging from “never” to “always”). For example, “I allow my child to choose which food to have for meals, I encourage my child to look forward to the meal.” The average score on each scale will be calculated, and a higher score will be considered to indicate a greater tendency for parents to feed their children in that style [80]. The overall Cronbach α is .75.

#### Parents’ Self-efficacy

Parents’ self-efficacy will be assessed using a previously used questionnaire [23], which has been translated back-to-back into simplified Chinese language. This questionnaire consists of 11 questions related to a child’s PA (4 items), DB (6 items), and sleep (1 item). For example, “How confident are you that you can promote healthy eating habits for your child?” Respondents will be asked to select from a 10-point Likert scale (ranging from “not at all” to “to a very high degree”). A higher score for the sum of the 11 questions will be considered to indicate a higher self-efficacy of parents regarding their children’s PA, DB, and sleep.

### Statistical Analysis

All statistical analyses will be conducted using IBM SPSS 27 (IBM Corp), and a 2-sided *P* value <.05 will be considered statistically significant. Baseline characteristics between the intervention group and control group will be compared using the chi-square test for categorical variables and ANOVA for continuous variables. A mixed model, which accounts for missing repeated measures, will be adopted with a 2-level between-group factor (intervention and control) and 2-level within-group factor (postintervention and follow-up assessment) repeated measures analysis of covariance (RM ANCOVA) to examine whether the eHealth-based parenting intervention improves preschoolers’ PA, DB, and sleep compared to the findings in the control group.

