### Participant Recruitment and Eligibility Criteria

Parent-child dyads will be recruited from kindergartens in Guiyang, Guizhou Province, China, with the support of Sun Yat-sen University and Guiyang Preschooler Education College. The entire recruitment process will be school-based. Kindergarten teachers will be asked to send a message to the parents in their respective WeChat class group. The message will briefly introduce the objectives and significance of the study. Parents will respond “yes” or “no” regarding their intention or willingness to participate. Face-to-face meetings will be held to provide more details to those parents who agree to participate in the study, especially on measurements, and to clarify the benefits that parents will receive after the study. Parents will be asked to add the researcher’s WeChat and sign the informed consent at the end of parent meetings. The inclusion criteria are as follows: (1) parents are older than 21 years and have children aged 3-6 years (the age range from 3 to 6 years has been found to be a strong predictor of future health) [51], (2) parental commitment to participate in the overall 6-month intervention, (3) parents have access to mobile technology, (4) parents and children are healthy (referring to a state of physical, mental, social, intellectual, and emotional well-being and the absence of disease) based on a health assessment performed by the kindergarten on the commencement day of a new semester, and (5) parents reside with participating children for at least 4 days a week in order to adequately expose the children to the parent-based intervention.

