### Randomization

Once participants are recruited and baseline measurements are collected, participants will be randomly allocated to either an intervention group (eHealth group) or a control group (traditional group) in a 1:1 ratio through a computer-generated list, using the statistical software SPSS (IBM SPSS 27, IBM Corp). The randomization will be conducted by a researcher who is blinded to the intervention recruitment and delivery. Random allocation to either the eHealth group or the control group will not be informed to parents.

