### Intervention Procedure

The eHealth intervention comprises 12 interaction modules, including PA (n=4), DB (n=4), and sleep (n=4). Each module will be rotated weekly to reduce the order effect on the outcome variables during the 12-week intervention period (ie, PA, diet, sleep, PA, diet…). Given that previous social media studies have indicated that 5 to 9 members in a group will produce the desirable group interactive effect [55], the participants will be grouped into 26 WeChat groups (8 members involved in each WeChat group) by the researchers according to the sample size calculation. Given that a facilitator has been found to be important to potentially make the intervention more individualized and may be successful in behavioral change [56], a teacher with expertise in PA, DB, and sleep who is working in the kindergarten will act as a facilitator, also known as a “captain,” in each WeChat group. Facilitators will be trained in a 5-hour workshop before the intervention and will be blinded to the study objectives. They will be responsible for sending videos; facilitating group interactions; responding to questions from parents; helping parents establish PA, diet, and sleep goals for their children; and providing feedback. Parents in each WeChat group will receive 2 self-monitoring text messages, and they will be required to provide a “yes” or “no” response. The first message will be sent as a feedback message to evaluate the progress toward the child’s weekly goal in the middle of the week. An “N” response may elicit a skill-building response to adjust the goal or adopt alternatives to achieve the goal (eg, try offering the same vegetable many times in different ways). If the parent responds “Y,” the facilitator will generate a message to reinforce positive behaviors, such as “Be proud of yourself, you’re getting your child off to a healthy start!” The second self-monitoring message will be sent on the weekend to assess goal attainment for the weekly target behavior before the new weekly theme is introduced. Figure 3 illustrates the intervention process of each module [57,58]. Multimedia Appendix 1 indicates what specific content will be shared.

Consistent with SCT [52], the content of each module will follow 4 steps (Figure 2 illustrates the intervention process of each module) as follows:

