### Sample Size

A recent systematic review and meta-analysis indicated a small but significant effect size for interventions to improve the PA of children aged younger than 5 years [69]. Interventions that aimed to enhance DB and reduce sleep problems among preschoolers had small to medium effect sizes [9,70]. Based on the information, a priori analysis will be conducted using G*power 3.1.9.6 [71]. A minimum sample size of 82 parent-child dyads in the intervention and control groups separately is required to detect a small effect size (*d*) of 0.3 with a power of 0.80 under the condition of an α level of .05. Considering a 20% potential attrition rate, 206 parent-child dyads in total are needed.

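### The eHealth arm is treated in facilitator-led WeChat groups of 8, but neither the stated model nor the sample size allows for it: if outcomes within a group are positively correlated, standard errors are too small and type I error exceeds 5%.

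*Protocol article*

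**What the plan says.** **Unit of randomisation.** Under Participant Recruitment and Eligibility Criteria, "Parent-child dyads will be recruited from kindergartens in Guiyang". Under Randomization, "participants will be randomly allocated to either an intervention group (eHealth group) or a control group (traditional group) in a 1:1 ratio". Allocation is therefore by dyad, not by kindergarten or class.

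**Delivery.** Under Intervention Procedure, parents are placed in WeChat groups of 8, a size chosen because earlier work suggested that groups of 5 to 9 interact well. In each group "a teacher with expertise in PA, DB, and sleep who is working in the kindergarten will act as a facilitator". This person sends the videos, leads discussion, helps set goals and gives feedback. The section gives 26 groups. Under Control Group, control dyads receive a weekly pamphlet and no interactive components.

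**Analysis.** Under Statistical Analysis, "A mixed model, which accounts for missing repeated measures, will be adopted with a 2-level between-group factor (intervention and control"), together with a two-level within-group factor (postintervention and follow-up) in a repeated measures ANCOVA, and "a 2-sided *P* value <.05 will be considered statistically significant". No WeChat-group, facilitator or kindergarten term is named.

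**Sample size.** The starting figure is "A minimum sample size of 82 parent-child dyads in the intervention and control groups separately". The section ties it to d = 0.3, 80% power and alpha 0.05. After the allowance for dropout it reads: "Considering a 20% potential attrition rate, 206 parent-child dyads in total are needed". The inputs are effect size, power, alpha and attrition; there is no ICC and no design effect.

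**The concern.** This is a partially nested design: individual randomisation, with one arm then treated in groups. Parents in one WeChat group share a facilitator and are meant to learn from each other, so peer interaction is a planned mechanism and some positive correlation within groups is to be expected. The repeated-measures part of the stated model deals with correlation within a child over time. It does not deal with correlation between children whose parents share a group.

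If that correlation is left out, the mean of the eHealth arm is treated as more precise than it is. Confidence intervals are then too narrow and the test rejects too often under the null, for the primary outcome and for every secondary outcome that carries a group effect. A sample size with no design effect overstates power for the same reason.

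**Working it through.** **Inputs from the protocol.** Two-sided alpha 0.05; 82 dyads per arm analysable; 20% attrition; 206 in total, so 103 per arm; WeChat groups of m = 8.

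**Assumptions.** The ICC is not given; 0.01 to 0.10 is used. The number of eHealth groups is inferred: 103/8 = 12.9, so about 13. The 26 stated groups would hold 26 × 8 = 208 dyads, which is the whole sample rather than one arm. Spread over the eHealth arm alone they would hold 103/26 ≈ 4 each, not 8.

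**The plan's own figure.** The attrition step reproduces: 82/0.8 = 102.5, rounded up to 103 per arm, 206 in total. The 82 does not follow from a two-sample comparison at d = 0.3, which needs 175 per arm two-sided (176 by exact t). A total of 164 is reproduced by a within-between interaction with f = 0.10, three measurements and correlation 0.5, but the protocol states none of these inputs. That is a separate question. What matters here is that every variant tried treats dyads as independent. Below, 82 per arm is taken as the independent-data requirement.

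**Formulas.** The design effect applies in the eHealth arm only: DE = 1 + (m − 1) × ICC. With equal arms, the variance of the difference is multiplied by V = (DE + 1)/2. The type I error of the unadjusted test is 2 × [1 − Φ(1.96/√V)]. Nominal 80% power becomes Φ((1.96 + 0.84)/√V − 1.96). The number per arm is 82 × V, rounded up, then divided by 0.8.

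With m = 8:

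| ICC | DE | V | √V | Type I error | Power | Per arm | Total with 20% attrition |
|---|---|---|---|---|---|---|---|
| 0.01 | 1.07 | 1.035 | 1.02 | 5.4% | 78.6% | 85 | 214 |
| 0.02 | 1.14 | 1.070 | 1.03 | 5.8% | 77.3% | 88 | 220 |
| 0.05 | 1.35 | 1.175 | 1.08 | 7.1% | 73.4% | 97 | 244 |
| 0.10 | 1.70 | 1.350 | 1.16 | 9.2% | 67.4% | 111 | 278 |

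Worked row, ICC 0.05: DE = 1 + 7 × 0.05 = 1.35; V = 2.35/2 = 1.175; 1.96/√1.175 = 1.808, which gives 7.1%. At ICC 0.05 the true variance is thus about 18% larger than the model assumes, and at 0.10 about 35% larger. Put the other way, the model understates the true variance by 1 − 1/1.175 = 15% and 1 − 1/1.35 = 26%.

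**Simulation.** An unclustered two-sample test with 13 groups of 8 against 104 independent controls (40,000 replicates) gave 5.2%, 7.0% and 9.3% at ICC 0.01, 0.05 and 0.10. Attrition shrinks the groups: 82/13 ≈ 6.3 members makes V = 1.13 at ICC 0.05, not 1.175. Across group sizes from this to 8, and across simulation runs, the results are about 5.2-5.4% (ICC 0.01), 5.7-6.2% (0.02), 6.7-7.2% (0.05) and 8.3-9.5% (0.10).

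**Does covariate adjustment remove it?** No. A baseline-adjusted ANCOVA that ignored groups (15,000 replicates) gave 6.9% at ICC 0.05 and 7.8-9.1% at ICC 0.10.

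**The case against.** **The ICC is unknown.** This stands. At ICC 0 there is no excess, and at 0.01 it is about 0.4 percentage points. The outcome is accelerometer-measured activity in children, whereas it is the parents who are grouped, so the correlation may be small. A reader might infer that the 5% level is certainly breached, or breached badly; the documents support only the conditional statement and a range.

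**A condensed article may leave random effects to the analysis plan.** This stands in part. The Statistical Analysis section is silent on a group effect and does not exclude one. But it does name the factors and says what the mixed model is for, namely missing repeated measures. Run as described, the analysis ignores the grouping. The sample size inputs are likewise stated, without an ICC.

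**The 26 groups.** Taken literally, they could suggest that both arms are grouped, which would apply the design effect twice and give 9.2% instead of 7.1% at ICC 0.05. The Control Group section does not support this, because controls get no interactive components. Still, the 13 groups used here remain an inference until the two sections are reconciled.

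**Kindergarten.** A reader might infer that leaving out kindergarten also inflates type I error. It does not, because dyads are randomised individually. A simulation with 206 dyads in six schools (an assumed number) and school ICC 0.05-0.10, ignoring school, gave 5.1-5.3%. The omission costs precision only.

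**The simulated test is simpler than the planned model.** True. The ICC that matters is the one remaining after covariate adjustment, so the figures show the order of the effect and do not predict it exactly.

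**Conclusion.** The concern holds in conditional form. The plan describes group-based treatment in one arm, and its stated model and sample size make no allowance for it. Any positive within-group correlation makes the standard error of the arm difference too small and pushes type I error above 5%.

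Over assumed ICCs of 0.01 to 0.10, type I error runs from just above 5% to roughly 9%, and a design with 80% power under independence has about 79% down to 67%. These sizes rest on the assumed ICC, on groups of about 8 with about 13 in the eHealth arm, and on ungrouped controls. Uncertainty about the ICC is a reason to estimate and report it, not to leave the group term out. The Results section says that outcomes are still being analysed, so the model can be corrected before results are published.

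**What to change.** **Statistical Analysis.** Add a random intercept for WeChat group in the eHealth arm only, with each control dyad as its own singleton. Use Satterthwaite or Kenward-Roger degrees of freedom, because there are few groups. Report the estimated ICC for each outcome.

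**Sample Size.** Restate power with a design effect of 1 + (m − 1) × ICC applied to the eHealth arm only, over a stated range of ICCs. Recruitment is complete, so this corrects the reported power and not the number of dyads.

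**Intervention Procedure and Control Group.** Reconcile the 26 groups of 8 with a control arm that has no interactive components, and state how many groups the eHealth arm contained. The coding of controls as singletons depends on this.

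**Optional.** Adjusting for kindergarten may improve precision. It is not needed to protect type I error.

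**Cost.** A few lines of syntax and some wording. The researchers formed the groups, so membership should already be on file. Intervals become slightly wider and the stated power slightly lower.

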## Results

Parent-child dyads were recruited in September 2023. Baseline and posttest data collection occurred from October 2023 to March 2024. The follow-up data will be obtained in June 2024. The research team has completed data collection for 238 parent-child dyads and is currently analyzing the outcomes. The results of the study are expected to be published in 2025.

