**Methods:**

This 2-arm, parallel, randomized controlled trial comprises a 12-week intervention with a 12-week follow-up. A total of 206 parent-child dyads will be randomized to either an eHealth intervention group or a control group. Participants allocated to the eHealth intervention group will receive 12 interactive modules on PA, DB, and sleep, with each module delivered on a weekly basis to reduce the sequence effect on variable outcomes. The intervention is grounded in social cognitive theory. It will be delivered through social media, where parents can obtain valid and updated educational information, have a social rapport, and interact with other group members and facilitators. Participants in the control group will receive weekly brochures on PA, DB, and sleep recommendations from kindergarten teachers, but they will not receive any interactive components. Data will be collected at baseline, 3 months, and 6 months. The primary outcome will be preschoolers’ PA. The secondary outcomes will be preschoolers’ DB, preschoolers’ sleep duration, preschoolers’ sleep problems, parents’ PA, parenting style, and parental feeding style.

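### The article gives two unreconciled sizes (206 and 238 dyads) and a contradictory status for the six-month follow-up, and neither size gives the stated 80% power on the stated inputs

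*Protocol article*

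**What the plan says.** **Size.** The abstract (Methods) states: "A total of 206 parent-child dyads will be randomized to either an eHealth intervention group or a control group". The Sample Size section reaches the same total. Its base figure is given as "A minimum sample size of 82 parent-child dyads in the intervention and control groups separately is required". The inputs behind that figure are a standardised difference of 0.3, power of 0.80 and α of .05. The allowance for loss follows: "Considering a 20% potential attrition rate, 206 parent-child dyads in total are needed". The Statistical Analysis section sets two-sided testing at .05, and the Randomization section sets 1:1 allocation.

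**Status.** The Results section says recruitment took place in September 2023. It continues: "Baseline and posttest data collection occurred from October 2023 to March 2024". On T3 it then says: "The follow-up data will be obtained in June 2024". The next sentence reads "The research team has completed data collection for 238 parent-child dyads and is currently analyzing the outcomes".

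**Analysis.** The Outcomes section lists three assessments: baseline (T1), the end of the 12-week intervention (T2) and the end of the 12-week follow-up (T3). The efficacy model in the Statistical Analysis section is a repeated measures analysis of covariance with a "2-level within-group factor (postintervention and follow-up assessment"), so T2 and T3 enter one model. No interim or T2-only analysis is described.

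**The concern.** A reader of the eventual report needs one number for the size of this trial, with a power statement that goes with it. The article prints two numbers. It does not say whether 238 means recruited, randomised, or measured, or through which time point. The answer matters: if 238 were randomised and 20% are lost, about 95 per arm remain; if 238 are completers, more were randomised than is reported.

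The power statement matters too. The Discussion lists the sample size calculation among the strengths, as a guarantee of adequate power. A null result on physical activity would be read against that statement, so it should be true on the inputs given.

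The T3 conflict leaves open when outcomes were first examined. If the arms were compared at T2 before T3 was measured, that comparison lies outside the planned model. It would add a second chance of a positive claim, and the T2 result would be known while T3 was being collected.

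**Working it through.** **1. The two counts.** 238 − 206 = 32, and 32/206 = 15.5%.

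**2. Reproducing 206.** Inputs from the Sample Size section: 82 per arm, 20% attrition. 82/0.80 = 102.5, rounded up to 103 per arm, and 2 × 103 = 206. The inflation step is correct.

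**3. Reproducing 82.** Inputs: d = 0.3, power 0.80, two-sided α = .05. For two independent means, n per arm = 2(1.960 + 0.842)²/d² = 2 × 7.849/0.09 = 174.4, so 175; the exact noncentral t calculation gives 176. One-sided testing gives 139 by the exact method. The figure of 82 is not reproduced.

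**4. Power and detectable effect at each size.** Two-sample t test, noncentrality d√(n/2), equal arms assumed:

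| n per arm | What it represents | Noncentrality at d = 0.3 | Power at d = 0.3 | d detectable with 80% power |
|---|---|---|---|---|
| 82 | stated minimum | 1.92 | 48% | 0.44 |
| 95 | 238 randomised, 20% lost | 2.07 | 54% | 0.41 |
| 103 | 206/2 | 2.15 | 57% | 0.39 |
| 119 | 238/2 | 2.31 | 63% | 0.37 |
| 176 | needed for 80% | 2.81 | 80% | 0.30 |

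**5. What the planned model could add.** Take baseline as the covariate (the article does not name one) and assume a common correlation r among T1, T2 and T3. The variance of the T2–T3 average given baseline is then (1 + r)/2 − r² times the single-measure variance.
- r = 0.3: factor 0.56, so 0.56 × 174.4 = 97.7, or 98 per arm.
- r = 0.5: factor 0.50, so 87.2, or 88 per arm.

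Adjusting a single post-baseline measure has factor 1 − r². At r = 0.5 this is 0.75, giving 131 per arm; at r = 0.7 it is 0.51, giving 89. The answer therefore depends on correlations and on a choice of contrast, and the article gives neither.

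**6. A possible source of 82.** A repeated-measures group-by-time F test with f = 0.10 (equivalent to d = 0.2), two groups, three measurements and correlation 0.5 gives power 0.7998 at a total of 162 and 0.805 at 164, that is, 82 per arm. On that basis power is 0.89 at 206 and 0.93 at 238. None of these inputs is stated, f = 0.10 is not d = 0.3, and the planned within-group factor has two levels, not three.

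**7. The T3 status.** There are three possible readings of the Results section: the future-tense sentence is out of date; completed collection means T1 and T2 only; or outcomes are being analysed before T3. The text does not decide between them.

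**8. Size of the problem if the arms were compared at T2 first.** Each test is at two-sided .05, bivariate normal, with an assumed T2–T3 correlation r of 0.3 to 0.8.
- T2 followed by a separate T3 test: the correlation of the statistics is r, and the chance of at least one false positive is 9.5% (r = 0.3) to 7.8% (r = 0.8).
- T2 followed by the overall group effect of the planned model, equal weights: the correlation is √((1 + r)/2), or 0.81 to 0.95, and the chance is 7.8% to 6.5%.

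**The case against.** The strongest reply is that nothing harmful has been shown. The 82 per arm is given as a minimum, so enrolling more breaks no rule and raises power: from 57% to 63% in the two-group calculation, and from 0.89 to 0.93 under the unstated repeated-measures inputs. Recruitment is dated September 2023, before baseline measurement began in October, so the excess could not have been a response to trial results. The mismatch between 82 and d = 0.3 would exist even if exactly 206 had been enrolled. All of this stands. The power shortfall is therefore attributed here to the stated inputs and not to the extra dyads.

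A reader might also infer that a T2-only efficacy look is under way. The article does not say so. The status sentence does not name T2 and does not say that arms are being compared, and it reads equally well as an update made after June 2024 beside a sentence left unrevised. An unplanned look is something to rule out, not an established fact.

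Nor can it be said that the trial falls short of 80% under every analysis: the figures of 48% to 63% belong to an unadjusted two-group test.

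What the reply does not remove is that the two totals are unexplained, the two status sentences conflict if collection includes T3, and the stated inputs do not give the stated power.

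**Conclusion.** The point holds as an inconsistency in reported size and status, together with a power statement that is wrong as written. The totals differ by 32 dyads (15.5%). On the stated inputs, power in an unadjusted two-group comparison is about 48%, 57% and 63% at 82, 103 and 119 per arm, against a stated 80% that needs about 176. These figures assume equal arms and no covariate adjustment. The planned T2 and T3 model may do materially better, but the article does not give the assumptions needed to show it.

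The type I error figures (roughly 6.5% to 9.5%) apply only if a between-arm comparison was made before T3, and only over the assumed range of correlations.

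**What to change.** 1. State what 238 counts: dyads recruited, randomised and measured, per arm and at each of T1, T2 and T3. Reconcile it with 206 and say when and why the target was exceeded.
2. Restate power, or the detectable effect, for the actual number under the planned model. Name the contrast, the covariate, the assumed correlations and the attrition. If the unadjusted two-group basis is kept, report a detectable d of about 0.39 at 103 per arm or 0.37 at 119 (0.44 at the 82 minimum). Bring the claim of adequate power in the Discussion into line.
3. Correct the T3 sentence in the Results section, and its repetition in the abstract, so that the status of T3 is unambiguous.
4. State whether any outcome was compared between arms before T3 was complete. If it was, declare it as outside the planned model and say how the type I error is handled. If not, one sentence settles the matter.

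The cost is wording and one recalculation, with a power figure that may be less favourable. No further participants or measurements are needed.
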